#### **6.4. Withdrawal of individual subjects**

Subjects can leave the study at any time for any reason if they wish to do so without any consequences. The investigator can decide to withdraw a subject from the study for urgent medical reasons.

#### **6.5. Replacement of individual subjects after withdrawal**

New subjects will replace subjects that are withdrawn from the study.

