#### 4.4. Sample size calculation

The primary endpoint of this study is the change in gut flora and fat absorption.

For the sample size calculation the following formula was used:

$$N = 2 + (Z_{1-\beta} + Z_{1-\alpha/2})^2 \times \sigma^2 / (\mu_{GT} - \mu_{CONTROL})^2$$

Subject population size was calculated using G\*Power 3.1.2 where  $\alpha$  was 0.05,  $\beta$  was 0.95 using group mean body weight changes from past papers (12) to calculate the effect size, the population was finalized as 45 per group and an additional 5 (drop-out of 10%) will be included in the population size for any unforeseeable circumstances which may lead to subjects dropping out.

The calculated sample size will be:

|                    |           |           |
|--------------------|-----------|-----------|
| Means:             | u1 = 72.5 | u2 = 71.4 |
| Standard deviation | SD1= 1.4  | SD2= 1.7  |

Confidence interval is  $\alpha=0.05$ , for  $\beta=0.95$

$$N1 = N2 = 2 + (Z(1-\beta) + Z(1-\alpha/2))^2 \times \frac{(\sigma_1^2 + \sigma_2^2)}{(\mu_1 - \mu_2)^2}$$

45 people per condition (two conditions; green tea and placebo).

Taking a drop-out of 10% into account, 50 subjects will be included per condition and herewith 100 subjects will be included in the experiment.

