#### **6.6. Follow-up of subjects withdrawn from treatment**

Subjects withdrawn from treatment will not be followed-up after eventually handing over responsibilities to medical personnel.

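### Sections 6.5 and 6.6 replace withdrawn subjects and stop measuring subjects taken off treatment, so the randomised comparison may be lost, and drop-out is allowed for twice

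*Protocol*

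**What the plan says.** Four parts of the protocol bear on this.

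- **Section 6.4** lets a subject leave at any time and for any reason, and adds: "The investigator can decide to withdraw a subject from the study for urgent medical reasons".
- **Section 6.5** reads in full: "New subjects will replace subjects that are withdrawn from the study". It sets no limit, no cut-off in time and no rule for allocating the newcomer.
- **Section 6.6** reads: "Subjects withdrawn from treatment will not be followed-up after eventually handing over responsibilities to medical personnel". The section concerns withdrawal from treatment, whereas 6.5 concerns withdrawal from the study. Nothing links or separates the two.
- **Section 4.4** arrives at 45 per condition and then states: "Taking a drop-out of 10% into account, 50 subjects will be included per condition and herewith 100 subjects will be included in the experiment".

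Section 8.2 plans an ANOVA with the three visits as the within-subject factor. The protocol does not say which subjects enter it, or what happens to data already collected from someone who is replaced.

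**The concern.** Randomisation protects the comparison only if the people randomised are the people compared. Under 6.5 and 6.6 read together, a subject taken off treatment yields no further outcomes and someone else takes the place. A statistical analysis plan, if there is one, could define an analysis set or keep the week 6 data. It could not recover week 6 or week 12 faecal fat, gut flora or body weight that was never measured. The loss is fixed by these conduct rules in the protocol.

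Withdrawal related to treatment is plausible on the protocol's own figures. Section 5.1 gives three green tea capsules at each of three meals, each with more than 31.3 mg caffeine, so more than 9 x 31.3 = 281.7 mg a day. In the placebo the extract is replaced by cellulose. Sections 4.2 and 4.3 admit only people using at most 100 mg caffeine a day. The arms therefore differ in an exposure these subjects do not normally have, and loss need not be balanced or unrelated to outcome.

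The second matter is bookkeeping. If 10% loss is already built into 100 subjects, replacing every withdrawal compensates for the same loss again.

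**Working it through.** **1. Drop-out allowance (section 4.4).** Inputs: 45 per condition, 10% loss. 45 / (1 - 0.10) = 50 per condition, 100 in total. The protocol's figure reproduces (45 x 1.1 = 49.5 also rounds up to 50). With no replacement and 10% loss, 50 x 0.9 = 45 per condition complete, which is what the calculation asks for.

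**2. What replacement adds.** If every withdrawal is replaced until 100 complete, and replacements drop out at the same rate d (assumed), the number randomised is 100 / (1 - d), rounded up:

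| d | Randomised |
|---|---|
| 5% | 106 |
| 10% | 112 |
| 20% | 125 |

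At the protocol's own 10%, about 12 randomised subjects would lack outcomes after withdrawal. There would be 100 completers, 10 more than the 2 x 45 = 90 required.

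**3. Bias.** In one arm, let p be the fraction withdrawn and g the gap between the mean outcome of completers and the mean that withdrawn subjects would have had. The completer mean departs from the mean of all randomised subjects by p x g. The error in the arm difference is

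p(green tea) x g(green tea) - p(placebo) x g(placebo).

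- Equal p and equal g in both arms: 0.
- 10% loss in one arm only, g = 1 kg: 0.10 x 1 = 0.1 kg, and 0.1 / 1.1 = 9% of the planned difference.
- 10% loss in one arm only, g = 2 kg: 0.10 x 2 = 0.2 kg, and 0.2 / 1.1 = 18%.

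The planned difference is 72.5 - 71.4 = 1.1 kg (section 4.4). The 10% is the protocol's own rate. The 1 to 2 kg gap is an assumption, as the protocol gives nothing from which to estimate it. Replacement leaves the expression unchanged: if newcomers are subject to the same withdrawal process, those who complete have the same expected mean as other completers. The count is restored and the error remains.

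**4. Power with and without replacement.** SDs of 1.4 and 1.7 (section 4.4) give a root mean square of sqrt((1.96 + 2.89) / 2) = 1.557. Two-sided power at alpha 0.05 is approximately Phi(1.1 / (1.557 x sqrt(2/n)) - 1.96).

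- n = 45: Phi(3.35 - 1.96) = 91.8% (91.2% by the exact t-test).
- n = 50: Phi(3.53 - 1.96) = 94.2% (93.8% by the exact t-test).

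The second allowance therefore raises power slightly. It does not reduce it.

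**The case against.** **No completer analysis is stated.** This is correct. A reader might infer that the plan commits to analysing completers only, but no section says so, and analysis sets are commonly left to the SAP. Listwise deletion is what a classical repeated-measures ANOVA would do with a missing visit; here it remains an inference. The missing outcomes do not depend on that inference.

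**Section 6.6 may concern medical care only.** Its reference to medical personnel allows that reading, and nothing says that someone who skips capsules but still attends counts as withdrawn. On the other hand, section 7.3 requires every adverse event to be followed until it abates or is stable, so the medical-care reading sits badly with 7.3. No other section provides outcome visits after treatment stops. Either way the sections need reconciling.

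**Predictable allocation.** A reader might infer that a newcomer takes the vacated arm, so that allocation can be guessed. The protocol does not support this. Section 6.5 gives no allocation rule, section 6.2 names computerised randomisation and double blinding, and a newcomer could be freshly randomised. What stands is that the rule is unstated.

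**The bias may be nil.** This also stands: with similar loss and similar gaps in both arms it is 0. A larger figure, such as 0.20 x 2 = 0.4 kg (36% of 1.1), needs 20% loss confined to one arm, twice the protocol's rate, and a gap larger than either planned SD. The estimates also cover body weight only. None is available for gut flora or faecal fat.

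**Conclusion.** The point holds in this form. Sections 6.5 and 6.6 do not separate stopping treatment from leaving the study, leave later outcomes uncollected and fill the place with someone else. The comparison is then at risk of not covering everyone randomised, and replacement does not cure that. For body weight the bias runs from 0 to about 0.2 kg, or 0 to 18% of the planned 1.1 kg, at 10% loss. The upper end assumes wholly one-sided loss and a 2 kg gap.

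The double allowance costs efficiency and clarity only. It leaves open whether 100 is the number randomised or the number completing: at 10% loss, 100 randomised or about 112.

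**What to change.** - **Sections 4.4 and 6.5:** state that 100 is the number randomised, and limit replacement to subjects who leave before randomisation. The 10% allowance then does its work once.
- **Section 6.6:** separate stopping capsules from leaving the study. Invite subjects who stop capsules to the scheduled week 6 and week 12 measurements unless they withdraw consent. This changes no rule on when treatment stops, and the right to leave in section 6.4 is untouched.
- **Section 8.2 or the SAP:** analyse all randomised subjects as allocated, with a mixed model that uses every available visit. The model alone is not enough, because without outcomes after stopping it must assume that the missing values are predictable from the observed ones.

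The cost is wording plus some visit effort for subjects who have stopped, since each visit carries a three-day faeces collection and the ventilated hood, with deuterium dilution added at week 12. About 45 instead of 50 per condition would complete, and two-sided power on the protocol's inputs falls from about 94% to about 92%. The protocol should state this. Both figures lie below the stated 95%; that mismatch is a separate issue in section 4.4 and not a reason to keep replacement.

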#### **6.6. Follow-up of subjects withdrawn from treatment**

Subjects withdrawn from treatment will not be followed-up after eventually handing over responsibilities to medical personnel.

## **7. SAFETY REPORTING**

### **7.1. Section 10 WMO event**

In accordance to section 10, subsection 1, of the WMO, the investigator will inform the subjects and the reviewing accredited METC if anything occurs, on the basis of which it appears that the disadvantages of participation may be significantly greater than was foreseen in the research proposal. The study will be suspended pending further review by the accredited METC, except insofar as suspension would jeopardise the subjects' health. The investigator will take care that all subjects are kept informed.

### **7.2. Adverse and serious adverse events**

Adverse events are defined as any undesirable experience occurring to a subject during the study, whether or not considered related to the experimental intervention. All adverse events reported spontaneously by the subject or observed by the investigator or his staff will be recorded.

A serious adverse event (SAE) is any untoward medical occurrence or effect that at any dose:

- results in death;
- is life threatening (at the time of the event);
- requires hospitalisation or prolongation of existing inpatients' hospitalisation;
- results in persistent or significant disability or incapacity;
- is a congenital anomaly or birth defect;
- is a new event of the trial likely to affect the safety of the subjects, such as an unexpected outcome of an adverse reaction, lack of efficacy of an (investigational medicinal product) IMP used for the treatment of a life threatening disease, major safety finding from a newly completed animal study, etc.

All SAEs will be reported through the web portal *ToetsingOnline* to the accredited METC that approved the protocol, within 15 days after the sponsor has first knowledge of the serious adverse reactions.

SAEs that result in death or are life threatening should be reported expedited. The expedited reporting will occur not later than 7 days after the responsible investigator has first knowledge of the adverse reaction. This is for a preliminary report with another 8 days for completion of the report.

**7.3. Follow-up of adverse events**

All adverse events will be followed until they have abated, or until a stable situation has been reached. Depending on the event, follow up may require additional tests or medical procedures as indicated, and/or referral to the general physician or a medical specialist.

## **8. STATISTICAL ANALYSIS**

### **8.1. Descriptive statistics**

Data will be presented as means  $\pm$  standard error of the mean (SEM).

The four groups will be stratified according to the number of males and females, BMI, age and the differences between these groups will be checked with the use of a factorial analysis of variance (ANOVA). P-values for these for these differences were, respectively, >0.9 for sex distribution and BMI, >0.8 for age, >0.5 for weight loss.

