## 4. STUDY POPULATION

### 4.1. Population

Subjects from the student population will be recruited by advertisements on notice boards at Maastricht University and in local newspapers. Healthy, non-smoking, males and females who are normal weight (Body Mass Index (BMI) 18.5-25 kg/m^2) or obese (BMI ≥30 kg/m^2) and aged between 18-50 yrs will be recruited for an initial screening, whereafter a total of 100 subjects (50 males and 50 females) will be included in the study. During the screening, subjects will undergo anthropometric and body composition measurements, and will complete questionnaires related to health, smoking behaviour, use of medication, alcohol consumption, probiotic consumption, physical activity, eating behaviour, mood and anxiety.

|              | Age 18-35 years |          | Age 35-50 years |          | Total |
|--------------|-----------------|----------|-----------------|----------|--------------|
|              | BMI 18.5-25     | BMI > 30 | BMI 18.5-25     | BMI > 30 |              |
| Male         | 12              | 12       | 12              | 12       | 48           |
| Female       | 12              | 12       | 12              | 12       | 48           |
| Total | 24              | 24       | 24              | 24       | 96    |

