### 6.2. Randomisation, blinding and treatment allocation

The study will be conducted in a randomized, placebo-controlled, double-blind parallel design with four randomly sequenced experimental conditions. Randomisation will take place using a computerized randomization program ('Randomizer' macro in Excel).

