### **8.2. Univariate analysis**

The Statistical Package for the Social Sciences (SPSS) will be used to perform univariate analyses. ANOVA will be performed to determine possible differences in gut flora, fat absorption, REE, activity and body composition between the four groups, with time (baseline, 6 weeks, 12 weeks) as the within-subject factor and group (normal weight-GT, normal weight-control, obese-GT, obese-control) as the between-subject factor. Post hoc, a Scheffe's *F* test will be applied. Statistical significance will be set at  $p < .05$ .

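### Section 8.2 makes baseline an outcome level and names no treatment contrast, and section 8.1 prints P-values that cannot come from this trial

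*Protocol*

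**What the plan says.** Section 8.2 fixes one model for gut flora, fat absorption, REE, activity and body composition: an ANOVA "with time (baseline, 6 weeks, 12 weeks) as the within-subject factor" and "group (normal weight-GT, normal weight-control, obese-GT, obese-control) as the between-subject factor", then Scheffé's test post hoc at the 5% level. It has no baseline covariate and no term for sex or age. It does not say whether the group main effect or the group-by-time interaction carries the treatment comparison.

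Sections 3.2 and 5.1 start the capsules after the baseline measurement. Section 6.1.1 defines the primary endpoints as changes (Firmicutes/Bacteroidetes ratio, total faecal fat, body weight), and section 4.4 sizes the trial on two conditions, green tea and placebo.

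Section 8.1 states "The four groups will be stratified according to the number of males and females, BMI, age" and that group differences will be checked by factorial ANOVA. It continues: "P-values for these for these differences were, respectively, >0.9 for sex distribution and BMI, >0.8 for age, >0.5 for weight loss". Section 6.2 says only that "Randomisation will take place using a computerized randomization program" and mentions no stratification.

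**The concern.** The baseline visit cannot carry a treatment effect, yet it is one of three response levels. The model is followed by a post hoc test on a four-level group factor, and such a test compares group means averaged over visits. An analyst following 8.2 literally could report that comparison as the treatment result. The attenuation could be large. For weight or body composition, a four-group test could also be significant only because two groups are obese and two are not.

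Even where the change contrast is used, the plan leaves unused the baseline value, sex and age, all of which are already collected.

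The printed P-values are a different matter. They state a balance between groups before anyone has been enrolled, and one of them conflicts with how the groups are defined.

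**Working it through.** The protocol gives no figure for this point other than the P-values in 8.1. The between-visit correlation r and all effect patterns below are assumptions.

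**1. What the group main effect estimates.** Averaged over baseline, week 6 and week 12, the treatment difference is (0 + d6 + d12)/3, where d12 is the week-12 effect.
- Equal effect at both visits: (0 + 1 + 1)/3 = 2/3.
- Linear growth: (0 + 0.5 + 1)/3 = 1/2.
- Week 12 only: (0 + 0 + 1)/3 = 1/3.

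A green tea minus placebo contrast of change from baseline recovers the full effect.

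**2. Precision of change against baseline adjustment at week 12.** With equal variances s² at both visits, the variance of change is 2s²(1 − r) and the ANCOVA residual variance is s²(1 − r²). The ratio ANCOVA/change is (1 + r)/2.

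| r (assumed) | 0.3 | 0.5 | 0.7 | 0.9 | 0.99 |
|---|---|---|---|---|---|
| ratio | 0.65 | 0.75 | 0.85 | 0.95 | 0.995 |

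**3. Simulation.** Four groups of 23 (46 per condition, against 45 planned as evaluable), 4,000 runs, r = 0.5, true effect 0.5 SD at both post-baseline visits. The outcome is the mean of those two visits, and BMI class is in the model.

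| Analysis of green tea vs control | Variance per subject | SE = √(2v/46) | Simulated SE | Mean estimate | Power |
|---|---|---|---|---|---|
| Average over three visits | (1+2r)/3 = 0.667 | 0.170 | 0.169 | 0.33 | 50% |
| Change from baseline | (1+r)/2 + 1 − 2r = 0.75 | 0.181 | 0.180 | 0.50 | 77% |
| ANCOVA | (1+r)/2 − r² = 0.50 | 0.147 | 0.148 | 0.50 | 91% |

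At r = 0.8 the powers are 40%, 99% and 99.7%. Change and ANCOVA are then almost equal; only the three-visit average still fails.

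**4. Omitting sex.** With a sex effect of 1 SD, constant over visits, and r = 0.5:
- change contrast: SE 0.18 and power 77% with or without sex, because the effect cancels within subject;
- ANCOVA: 89.5% without sex, 91.6% with it;
- three-visit average: power falls from 50% (no sex effect) to 35%.

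If sex and age explain a share R² of the variance of the *change*, omitting them inflates the SE by 1/√(1 − R²): 1.03 at 5%, 1.05 at 10%, 1.20 at 30%.

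**5. The BMI P-value.** Section 4.1 defines the groups by 18.5–25 and ≥30 kg/m², which do not overlap. Take deliberately close values: means 24 and 31, SDs 1.9 and 6, 25 per group. The between-group mean square is 100 × 3.5²/3 = 408.3 and the within-group mean square is (1.9² + 6²)/2 = 19.8. So F(3, 96) = 20.6 and P is about 2e-10. In 5,000 draws of 24 per group, the largest P was 1.4e-30 (uniform over 18.5–25 and 30–45), or 2.6e-11 with a long obese tail. A value above 0.9 across the four groups is not attainable.

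**6. The weight-loss P-value.** Section 4.2 requires weight stability (change below 3 kg in six months), no weight-loss phase precedes treatment, and change in body weight is a primary endpoint in 6.1.1. Weight loss is therefore not a baseline characteristic here.

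**The case against.** The strongest defence is that a time-by-group ANOVA contains a group-by-time interaction, and that endpoints defined as changes point to it. A contrast of changes is undiluted. A reader might infer from 8.2 that the planned treatment estimate is attenuated; the protocol does not support that, because nothing in it names the main effect as the treatment test. What stands is that nothing names the interaction either, and the Scheffé test on groups points the other way.

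A reader might also infer that precision is lost materially on every endpoint. That depends on r, which the protocol does not give. Near 0.99, plausible for body weight in weight-stable adults, the gain from ANCOVA is 0.5%. It could be material for faecal fat and the bacterial ratio if their correlations are moderate.

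It is tempting to say that if sex and age explain 20–40% of outcome variance, omitting them widens standard errors by 12–29%. That does not carry over to change contrasts, where effects constant over time cancel. BMI class, the third stratifier, is in the model through the group factor. The table in 4.1 has no treatment arm, so it shows recruitment quotas, not balance between arms.

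Nor does the plan rely on the baseline tests: 8.1 only checks differences, nothing in 8.2 depends on the result, and these P-values cannot affect a treatment estimate. BMI P>0.9 could also hold for green tea against placebo within a BMI class, though not before data exist.

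Finally, covariates are often left to an analysis plan, which is not shown. Here, however, the protocol states a specific model, and that model can be judged as written.

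**Conclusion.** The point holds in limited form.

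- **Unnamed treatment contrast.** Section 8.2 permits a main-effect reading that would estimate between one third and two thirds of the effect, depending on its time course, and that would mix in lean/obese differences. The change contrast has no such bias.
- **Unused baseline.** Against the change contrast, ANCOVA lowers the week-12 variance by 25% at r = 0.5, 5% at 0.9 and 0.5% at 0.99, assuming equal variances at both visits.
- **Sex and age.** Naming them as stratifiers and leaving them out of the model is inconsistent. The cost on change contrasts is small if their effects are constant over time.
- **Printed P-values.** They cannot be results of this trial, since nobody has been enrolled. The BMI value conflicts with the group definitions across the four groups, and the weight-loss value refers to no baseline variable. This part needs no assumption about r, and it is an error of text that leaves the treatment estimate untouched.

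The changes should be made before analysis. Nothing here shows that the design itself is unsound.

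**What to change.** In section 8.2, analyse weeks 6 and 12 as outcomes, with the baseline value of the same variable as covariate. Include treatment, BMI class, treatment by BMI class, sex, age, visit, treatment by visit, and treatment by BMI class by visit. The BMI-class interactions are needed because section 2 expects a larger change in the Firmicutes/Bacteroidetes ratio in obese subjects; a model without them could not test this. For total body water and waist-to-hip ratio, which the flow chart in 3.3 schedules only at baseline and week 12, use week 12 alone and drop the visit terms. Name the baseline-adjusted week-12 green tea minus placebo difference, with its 95% CI, as the treatment estimate.

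In section 8.1, delete the sentence with the P-values and the baseline significance tests, and describe baseline by group only. State in section 6.2 whether randomisation is stratified by sex, age and BMI class, so that 6.2 and 8.1 agree.

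The cost is wording and a few degrees of freedom. Every covariate is already collected, and no visit or measurement is added.
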